## Abstract

**Background:**

Telehealth has the potential to improve asthma management through regular monitoring of lung function and/or asthma symptoms by health professionals in conjunction with feedback to patients. Although the benefits of telehealth for improving asthma management have been extensively studied, the feasibility of telehealth for supporting asthma management in pregnant women has not been investigated. This study aims to evaluate the use of telehealth for remotely monitoring lung function and optimising asthma control during pregnancy.

**Methods:**

A randomised controlled trial comparing usual care with a telehealth program (MASTERY^©^) has been conducted. The intervention comprised a mobile application – *Breathe-easy*^*©*^ supported by a Bluetooth-enabled handheld device (COPD-6®), which was used for self-monitoring of lung function (FEV_1_, FEV_6_) twice daily, and recording asthma symptoms and medication usage weekly; and a written asthma action plan (WAAP). The primary outcome measure is change in asthma control measured using the Asthma Control Questionnaire (ACQ). Secondary outcomes include changes in mini-Asthma Quality of Life Questionnaire (mAQLQ) score, lung function, asthma-related health visits, days off work/study, and oral corticosteroid use. Outcome data were collected at baseline, 3 months and 6 months by a research assistant masked to group allocation. Maternal and neonatal outcomes were also collected post-partum.

**Discussion:**

This is the first study to evaluate the application of telehealth to optimize asthma management in pregnant women. If effective, this telehealth program could improve asthma self-management by pregnant women which may reduce the maternal and fetal risks of poorly controlled asthma during pregnancy.

**Trial registration:**

Australian New Zealand Clinical Trials Registry (ACTRN 12613000800729) 17 July 2013

**Electronic supplementary material:**

The online version of this article (doi:10.1186/s12890-015-0082-3) contains supplementary material, which is available to authorized users.

## Background

Asthma is the most common obstructive pulmonary disease that occurs during pregnancy and may complicate pregnancy [1–4]. Previous studies have demonstrated that asthma during pregnancy improves in slightly more than a quarter of patients, but worsens in slightly more than one-third, and remains unchanged in one-third [5]. Poorly controlled asthma increases the risk of poor outcomes such as pre-eclampsia, fetal growth restriction, preterm birth and need for caesarean delivery [6–9]. Given the lifelong health decrements associated with these outcomes, an approach to optimise monitoring and treatment of asthma could have major short and long term public health benefits.

Education and regular monitoring by a pharmacist-led multidisciplinary team has been shown to improve asthma control during pregnancy [10]. Asthma management programs for pregnant women which involve regular monitoring of lung function and assessment of asthma symptoms appear to be effective in reducing asthma exacerbations [11, 12]. However, further studies are required to determine the most effective and safe interventions for managing asthma in pregnancy to improve maternal and neonatal outcomes [12].

Better asthma control can be achieved if patients are involved in self-management. This includes self-monitoring of asthma symptoms or lung function and following written asthma action plans while maintaining regular contact with their health professionals [13]. Telehealth supports asthma management through patient education, adherence support, telephone follow-up and remote monitoring [14]. Telehealth interventions have shown significant clinical improvement and potential benefits in patients with asthma, including: reduced time to access healthcare services and reduced cost linked to travelling; earlier detection of worsening asthma (e.g. exacerbations), and reduced healthcare visits/hospitalisations due to asthma [15–18]. Lung function data derived from telehealth assessment studies were comparable to those collected under supervision by healthcare professionals and thus valid [19, 20]. Telehealth programs also appeared to be feasible for asthma patients, as compliance with monitoring was high and most patients found the equipment easy to use [21].

Telehealth studies show potential benefits for asthma management in the general population [22]. However the feasibility of telehealth for supporting asthma management in pregnant women has not been investigated to date. Pregnant women with asthma are young and are likely to be willing to use new technology to assist self-management of their asthma. Hence, the present study will examine the potential for enhanced asthma management in pregnancy through a telehealth program.

The study aims to evaluate the efficacy of a telehealth intervention supported by a handheld respiratory device and a written asthma action plan (WAAP) for management of asthma in improving asthma control during pregnancy. We hypothesised that the telehealth intervention group will have better asthma control as measured by the Asthma Control Questionnaire (ACQ) score changes than the control group at three and six months from baseline.

## Methods

### Study setting

Participants were recruited when attending scheduled antenatal visits at two large maternity hospitals in Melbourne, Australia (Mercy Hospital for Women and The Royal Women’s Hospital); each hospital has approximately 6000 births per year.

### Study design

The study was designed as a prospective multi-centre single-blinded randomised controlled trial (RCT) with outcome assessors masked to group allocation at follow-up assessments. The flow of participants is illustrated in Fig. 1. The total duration of the intervention was 6–8 months depending on timing of the first antenatal visit and enrolment in the study. Both groups were followed up throughout pregnancy and the outcomes are being compared at three and six months from baseline to evaluate the efficacy of the intervention.

**Fig. 1 Fig1:**
[figure not shown]
Participant flow diagram

### Inclusion and exclusion criteria

Eligibility for this trial included pregnant women with asthma who had used any inhaled bronchodilator or anti-inflammatory agent for asthma within the previous 12 months, were attending antenatal clinics in first or second trimester, aged 18 years or older and able to communicate in English. Those under specialist care for severe/difficult asthma were excluded. Women who are not already in possession of or have not used a smart mobile phone were considered ineligible to participate. This was confirmed by directly asking pregnant women about their mobile phone usage.

### Trial recruitment

The following methods of identification and recruitment of participants were used:One of the researchers (EZ) or research staff searched the outpatient files and screened the medical records of pregnant women with asthma scheduled to have a clinic visit on the following day by reviewing GP referral letters and/or notes from previous clinic consultations. Eligible women were approached for recruitment after clinic visit completion. On each day the researcher/research staff also searched for potential participants by screening medical records of women who were reviewed by the midwives or medical staff in the antenatal clinics.At one of the sites (the Mercy Hospital for Women), a letter of invitation including a brief explanation of the study together with their antenatal appointment letter was posted to all pregnant women newly registered with the antenatal clinic. At their first clinic visit, the researcher approached each eligible woman and sought interest in participation.Advertising posters about the study were placed in the antenatal clinics of participating hospitals and on the websites of the National Asthma Council and the Asthma Foundation of Victoria. Participant explanatory statements and expression of interest forms were also made available. Potential participants had access to the information and were asked to leave their contact details to allow one of the researchers to contact them.

If the woman agreed to participate, written informed consent was sought.

### Group allocation

Recruited participants were allocated to intervention or control groups on a 1:1 basis, stratified by their asthma severity. Asthma severity was assessed in accordance with the National Asthma Council Australia (NAC) Asthma Handbook classification based on their current asthma medications and symptoms [23]. Participants were classified into two groups: 1) Intermittent – mild asthma: using relievers only (e.g. salbutamol); 2) moderate – severe asthma: using any regular inhaled corticosteroids/ preventers/ symptom controllers or their combinations.

Allocation was concealed using the sealed opaque envelope technique. Random blocks of four and six were chosen and random numbers were generated using a random allocation software program [24] by an external researcher not involved in the study. The allocation sequence was known to this researcher only. At the time of recruitment, the investigator (EZ) opened the numbered envelope and allocated each participant to the control (usual care) group or the intervention (MASTERY) group. The outcome assessors were masked to the participant group allocation at follow-up assessments.

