### Sample size

A sample size of 28 per arm is sufficient to detect the minimum clinically important difference in ACQ score of 0.5 or more between treatment groups using a standard deviation of 0.66 [10, 28, 29]. We estimate, conservatively, that by 3 months, there will be an improvement of at least 0.5 in the ACQ score in the intervention arm and that the control arm could exhibit a very small improvement or no improvement at all in the ACQ score. If these improvements are sustained at 6 months, then with 28 evaluable subjects in each arm, and assuming an independence model for measurement variation, and an intraclass correlation of 0.5 (equivalent to a within patient variance of 0.218 when the total variance is 0.66^2^ = 0.436), the F-test, conducted at the 5 % significance level will have at least 80 % power to detect a treatment by time interaction effect. If these conjectured improvements by month 3 are not durable and the scores return, on average, to their baseline levels at 6 months, then both the F-test for the interaction and the two-sided *t*-test comparing the two arms at month 3 at the 5 % level of significance will continue to have at least 80 % power. To allow for approximately 25 % attrition, the target sample size has been inflated from 28 per arm to 36 participants per arm. The study is, however, not powered to detect differences in the secondary outcomes.

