### Data analysis

All analyses will be performed using SAS version 9.4 (SAS Institute, Cary, NC, USA) and SPSS version 19.0 (IBM SPSS Statistics for Windows, Armonk, NY). The baseline characteristics of the two groups will be compared using Student’s *t*-test for normally distributed continuous variables, Mann-Whitney ‘U’ test for non-normally distributed continuous variables and chi-square or Fisher’s exact test as appropriate for categorical variables. The primary analysis will be performed according to the intention to treat (ITT) principle on the “full analysis set”.

Primary inferential analyses will be conducted using a mixed effects model for the ITT population. This model will include treatment group and time as fixed effects with an interaction between treatment and time to ascertain if the groups behave differently over time. All observed data will be included in the analysis, with the mixed-effects models, fitted by residual maximum likelihood (REML) assuming non-informative dropout such that the probability of dropout may depend on a participant’s previous response but not on current or future responses. In supportive analyses, changes in the primary outcome from baseline to 3 and 6 months will be compared between groups using linear regression modelling adjusting for baseline scores. Baseline demographic and clinical factors that appear to be different will be included as potential covariates in all regression models.

We will also compare the proportion of participants whose ACQ score improves more than 0.5 (MCID) over the study period, the proportion in whom asthma remained “not well controlled’ (ACQ score 1.5 or greater) and those whose asthma was “well controlled” (ACQ score less than 1.5) at each time point [26]. Secondary outcomes will be summarised using descriptive statistics and analyses will be performed using the methods described above.

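### Randomisation was stratified by asthma severity, but the stated model leaves the stratum out and the covariate rule would not normally bring it back; the cost falls mainly on single-visit comparisons, not on the primary interaction test

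*Protocol article*

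**What the plan says.** Under Group allocation, the Protocol article states that participants were "allocated to intervention or control groups on a 1:1 basis, stratified by their asthma severity". There are two strata, women on relievers only and women on any regular preventer or controller, with random blocks of four and six.

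Under Data analysis, the primary model is given by its terms: "This model will include treatment group and time as fixed effects with an interaction between treatment and time". Severity is not among them. The supportive analysis takes changes in ACQ from baseline to 3 and 6 months, "compared between groups using linear regression modelling adjusting for baseline scores". One rule governs all other covariates: "Baseline demographic and clinical factors that appear to be different will be included as potential covariates in all regression models". The same section plans comparisons of the proportion of women who improve by more than the minimal important difference, and of the proportions with and without good control at each time point. No stratum adjustment is stated for these.

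Under Sample size, the test on which power is claimed is the interaction: with 28 evaluable women per arm the F-test "will have at least 80 % power to detect a treatment by time interaction effect".

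**The concern.** A factor that restricts the randomisation and predicts the outcome belongs in the analysis. Blocking within strata holds the arms nearly equal on severity, so severity contributes almost nothing to the true sampling variance of a between-arm difference. A model without severity still counts it as residual noise. Standard errors are then too large and tests too conservative for any contrast in which severity has not already been removed.

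The covariate rule does not repair this. It selects on observed imbalance, which stratification is designed to prevent, so the one factor that the investigators chose to stratify on is among the least likely to be admitted. Chance imbalances in other factors can enter after the data have been seen. With 28 evaluable women per arm, avoidable noise is worth removing. What has to be settled is which of the planned analyses are affected, and by how much.

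**Working it through.** **Inputs.** From Sample size: difference 0.5, SD 0.66, total variance 0.436, intraclass correlation 0.5 ("equivalent to a within patient variance of 0.218"), 28 evaluable per arm, 36 recruited per arm, 5% level. From Data collection and follow-up: baseline, 3 and 6 months. Not given: the share R² of ACQ variance explained by severity. I take 0 to 0.4 as an assumption.

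**1. The plan's own figures.** n per arm = 2(1.96 + 0.8416)² × 0.66² / 0.5² = 2 × 7.849 × 0.4356 / 0.25 = 27.35, so 28, as stated. Power at 28 is 80.9% by the normal approximation and 79.5% by noncentral t. For the interaction with arm differences (0, 0.5, 0.5), the squared deviations from their mean sum to 1/9 + 1/36 + 1/36 = 1/6. The noncentrality is (28/2) × (1/6) / 0.218 = 10.70 on 2 and 108 degrees of freedom, and power is 83.1%. The non-durable pattern (0, 0.5, 0) gives the same sum and the same power. The stated figures are reproduced.

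This also fixes what the test is. A sustained effect produces an interaction only if baseline is one of the time levels, so the primary test compares within-woman change.

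**2. Primary interaction test, severity effect constant over time.** Such an effect subtracts out of follow-up minus baseline. The standard error of the contrast is √(2 × 2 × 0.218 / 28) = 0.1765, which contains only within-patient variance.
- Complete data, 28 per arm: 0.1765 with or without the stratum for every R² from 0 to 0.4 (ratio 1.000).
- 36 per arm, with an assumed 4 women per arm lost after baseline and 4 after month 3 (8/36 = 22.2%): the ratio with to without the stratum is 0.996 (month 3) and 0.995 (month 6) at R² = 0.2, and 0.990 and 0.985 at R² = 0.4. The largest gain is about 1.5%.
- Simulated type I error without the stratum (8000 runs): 0.050, 0.053 and 0.052 at R² = 0, 0.2 and 0.4. The test is not conservative.

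**3. Between-arm comparison of mean ACQ at one visit.** The model variance is 2σ²/n; under stratum balance the true variance is 2σ²(1 − R²)/n. The standard error is therefore too large by the factor 1/√(1 − R²), and the actual error of a nominal 5% test is 2[1 − Φ(1.96/√(1 − R²))].

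| Assumed R² | √(1 − R²) | SE too large by | Actual error |
|---|---|---|---|
| 0.05 | 0.975 | 2.6% | 4.4% |
| 0.10 | 0.949 | 5.4% | 3.9% |
| 0.20 | 0.894 | 11.8% | 2.8% |

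Simulation of the month-3 t-test agrees in direction and rough size: type I error 0.032 at R² = 0.2 and 0.011 at R² = 0.4, against about 0.05 with the stratum. At R² = 0.2, power is 81.9% without the stratum and 87.5% with it.

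**4. Supportive regression adjusted for baseline score.** At R² = 0.2, the standard error is 0.1536 without the stratum and 0.1471 with it (0.1536/0.1471 = 1.044). Type I error is 0.046 against 0.053, and power 90.4% against 91.8%. At the extreme R² = 0.4, the standard errors are 0.1533 and 0.1353.

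**5. Interaction test if severity predicts change.** If stratum-by-time explains 5%, 10% or 20% of within-patient variance (assumed), including it multiplies the standard error by 0.975, 0.949 or 0.894. F-test power rises from 83.1% to 85.1%, 87.1% or 90.8%. These powers keep 108 denominator degrees of freedom and ignore the two that the term uses.

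**The case against.** A reader might infer that the primary test itself is conservative and its standard error inflated because the stratum is missing. The documents do not support that. The test on which the trial is powered is a within-woman contrast, and step 2 shows that a constant severity effect drops out of it.

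It can also be said that the single-visit figures describe an analysis that Data analysis does not plan for the ACQ score: the month-3 t-test appears only under Sample size, and the supportive regressions adjust for baseline score, which already carries much of what severity predicts. This largely stands. The single-visit figures still apply to that t-test and to any visit-specific arm difference read from the mixed model, and they indicate the direction for the proportions at each time point. I have not calculated a size for the proportions.

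The size depends on an R² that the article does not report and that could be near zero. Nothing in the article shows that severity predicts change. Both points stand, so the size is conditional.

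The covariate rule does not strictly bar the stratum: incomplete blocks and about 25% attrition can leave some imbalance. True, but the rule would not normally admit it.

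Finally, an unseen analysis plan might add the stratum. It might, but the article does not leave the matter open. It states the model terms and the rule by which anything else enters. Any error is in the safe direction, with no bias and no excess of false positives.

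**Conclusion.** The concern holds in a limited form. The stated primary model omits the randomisation stratum, and the stated covariate rule would not normally restore it.

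- **Primary treatment-by-time test:** valid. Its standard error is unchanged with complete data and falls by at most about 1.5% under the assumed dropout, provided that the severity effect is constant over time. It loses precision only if severity predicts change in ACQ.
- **Single-visit comparisons of the score:** conservative, with standard errors 2.6%, 5.4% or 11.8% too large at an assumed R² of 5%, 10% or 20%.
- **Supportive regressions:** a small loss, about 4% in the standard error at R² = 0.2.

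The omission is certain from the text. Every size except the exact cancellation rests on assumed R² values. This is an inexpensive gain in precision and in pre-specification, not a threat to the trial's validity.

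**What to change.** Name the severity stratum as a fixed term, regardless of observed imbalance:
- in the primary mixed model, the stratum and stratum-by-time. The main effect alone does nothing for the interaction test with complete data, so the time interaction is the part that can help it;
- in the supportive regressions of change, the stratum beside the baseline score;
- for the responder and asthma-control proportions, a stratum-adjusted comparison (Mantel-Haenszel or logistic), with the effect measure stated, since an adjusted odds ratio is not the same quantity as an unadjusted one.

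The cost is one binary variable, already recorded for every woman in order to randomise her. In the mixed model it uses 3 degrees of freedom with three time levels: 1 for the stratum and 2 for stratum-by-time. The sample size and power figures need no change. Trial status reports that analysis is under way, so the choice should be recorded now and its date reported with the results.

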### Control and intervention group

#### Intervention: MASTERY group

The trial evaluated an intervention involving a telehealth program supported by a Bluetooth-enabled handheld spirometer COPD-6® (model number 4000, Vitalograph Ltd, Ennis, Ireland) and a WAAP. Women allocated to the intervention group were provided with a COPD-6® and a loaned smart mobile phone with the specifically designed *Breathe-easy*^©^ application installed on it. Each participant measured their lung function (FEV_1_ and FEV_6_) daily using the COPD-6® device and recorded asthma symptoms and asthma medication usage in the *Breathe-easy*^©^ application weekly. The daily lung function data were uploaded to a central server where the researchers, participants and their health professionals had secure access to the data. The participants’ health professionals were contacted by one of the researchers, a trained asthma educator (EZ), if any medication changes or unscheduled asthma-related visits were needed.

A WAAP consistent with NAC guidelines was designed for each participant based on information obtained at baseline. The WAAP contained instructions on which medications to take when feeling well, how to recognise worsening asthma, what to do when symptoms are getting worse and what to do in the event of an acute attack, including a first aid plan. Each participant received an automated weekly message regarding their asthma status based on the *Breathe-easy*^©^ algorithm that was designed based on NAC [23] and Global Initiative for Asthma (GINA) guidelines [25] (Additional file 1: Table S1). An automated weekly message of overall asthma control status was displayed as ‘well-controlled’ (score 0, green zone), or ‘not well controlled’ (score 5, yellow zone and score 6, orange zone) to encourage participants to follow their agreed asthma action plan and/or contact their health professional the next working day if there was no improvement. If the asthma control status was displayed as ‘very poorly controlled’ (score 7–15, red zone), patients were prompted to follow their agreed asthma action plan and contact their health professional on the same day. The flow of the study is described in Fig. 2 and the details of the intervention are illustrated in Fig. 3.

